#### Neuroimaging

All subjects will be scanned on a SIEMENS Prisma or Prismafit 3T MRI system. Scanner type will be consistent within subjects. The following scans will be acquired:

*T1 weighted MPRAGE structural image* (TR: 2300ms, TE: 3.03ms, FA: 8 deg, TI: 1100ms, voxel size: 1.0 × 1.0 × 1.0 mm, FOV: 256 mm; acquisition time: 5m21s).Neuromelanin-sensitive *turbo spin echo T1 weighted image* to quantify structural integrity of the substantia nigra and locus coeruleus (TR: 890ms, TE: 13ms, FA: 120 deg, voxel size: 0.2 × 0.2 × 3.0 mm, FOV: 220 mm; acquisition time: 6m48s).*Diffusion weighted image* to quantify free water volume in the substantia nigra (TR: 3000ms, TE: 74.40ms, FA: 90 deg, voxel size: 2.0 × 2.0 × 2.0 mm, acceleration factor: 3, diffusion directions: 104, B-values: 1000 and 2000s/mm^2^, FOV: 210 mm; acquisition time: 5m30s).Resting-state BOLD EPI (functional MRI) images (eyes open, fixation cross) will be acquired twice: before and after stress induction (multi-band 3 multi-echo 3, TR: 1500ms, TE: 13.4ms / 34.8ms / 56.2ms, FA: 75 deg, voxel size: 2.5 × 2.5 × 2.5 mm, FOV: 210 mm, 400 volumes; acquisition time: 10m18s).

Participants’ stress-reaction will be investigated by means of the *socially evaluated cold pressor task* (SECPT) [33]. Resting-state functional MRI will be acquired before and after stress-induction (see imaging details above*)*. A researcher unknown to the participant will enter the room to perform the stress-induction task. The participant is asked to immerse their foot in a box of cold water (1.8–2.2℃) and to try keeping it in for three minutes, unless it is unbearable to continue. The participant is told that their facial expressions are evaluated during the task. The researcher is instructed to refrain from giving any positive feedback during the task and to try to keep a neutral facial expression. The second part of the stress-induction continues once the cold pressor test is over and the participant’s foot is covered with a towel. During the second part of the task, the participant is asked to alternatively cite the alphabet from the back and front (Z-A-Y-B-X-C etc.), as fast and as accurately as possible. If they are too slow, the researcher asks them to speed up. If they are incorrect, the researcher asks them to start from the beginning. This task lasts 3 min. Subjective stress levels will be collected before and after stress-induction on a 10-point scale [1 (not stressed at all) − 10 (very stressed)].

#### Questionnaires

All questionnaires will be assessed online via CastorEDC.

*The Perceived Stress Scale* (PSS), a questionnaire consisting of 10 items, is used to measure perceived stress (range 0–40). It assesses how unpredictable, uncontrollable, and overloaded respondents experience their lives in the past month. Responses are given on a 5-point Likert scale. Studies have demonstrated good reliability of the PSS (Cronbach’s α = 0.78) [34].

The *Ruminative Response Scale* (RRS) is a 22-item questionnaire that measures the tendency to use ruminative thinking when being in a negative mood (range 22–88). Items are rated on a 4-point Likert scale. The Dutch RRS has been shown to have excellent internal consistency (Cronbach’s α = 0.90) [35].

The *Self-Compassion Scale Short Form* (SCS– SF) consisting of 12 items (range 12–84) is used to measure self-compassion on six scales: self-kindness, self-judgment, common humanity, isolation, mindfulness and over-identification. Items are scored on a 7-point Likert scale. A total self-compassion score is computed by reversing the negative subscale items and combining the subscale scores. Higher scores indicate more self-compassion. The psychometric properties of the Dutch SCS-SF have been shown to be good (Cronbach’s α = 0.87) [36].

We use a Dutch adaptation of the *General Self-Efficacy Scale* (GSES) [37].The GSES is a 10-item questionnaire (range 10–40) to measure general sense of perceived self-efficacy, which is thought to predict the ability to cope with adversity. Good reliability of the GSES has been reported (Cronbach’s α = 0.75–0.90) [38].

Positive appraisal style, the tendency to appraise potentially threatening situations in a positive way, has been proposed to be an important resilience mechanism, and therefore offers a potential target for stress-alleviating approaches [39]. The *Positive Appraisal Style Scale (PASS)*, based on the German 14 item PASS-process described by Petri-Romao and colleagues [40] will be used to measure positive appraisal style.

The *Five Facet Mindfulness Questionnaire* (FFMQ) is used to measure mindfulness skills [41]. The FFMQ consists of 39 items divided into 5 facets: observing, describing, acting with awareness, non-judging and non-reactivity. Each item has 5 answer options, where higher scores reflect more mindfulness skills (range 39–195). All facets of the Dutch version in a (non-PD) sample with depressive symptomatology have been shown to be reliable (Cronbach’s α = 0.73–0.91) [42].

Perceived social support will be measured using a Dutch translation of the brief *Perceived Social Support Questionnaire* (F-SozU K-6) [43], a 6 item questionnaire measuring perceived and anticipated social support on a 5-point Likert scale (range 6–30). The German F-SozU K-6 has been shown to have high internal consistency (Cronbach’s α = 0.90).

We assess quality of life using the *Parkinson’s disease questionnaire 39* (PDQ-39). This questionnaire consists of 39 items in 8 domains: mobility (10 items), activities of daily living (ADL, 6 items), emotional well-being (6 items), stigma (4 items), social support (3 items), cognitions (4 items), communication (3 items) and bodily discomfort (3 items). All items are scored on a 5-point Likert scale. Items are first summed and then linearly transformed to a 0–100 scale. The internal consistency has been shown to be high for all but one domain (Cronbach’s α = 0.71–0.91 for 7 of the 8 domains, and 0.59 for ‘bodily discomfort’) [44].

*Non-motor and motor complications* during daily living will be assessed by the MDS-UPDRS Ib and II [28], a 20 item questionnaire. PD related impairments are rated on a 5 point scale (0: normal – 4: severe).

Finally, adherence to the mindfulness intervention will be assessed using a Dutch version of the 12-item *Mindfulness Adherence Questionnaire* (MAQ) [22]. Items are scored on a 7-point Likert-scale. This questionnaire measures the duration and frequency with which both formal and informal mindfulness exercises are performed; higher scores reflect a higher practice frequency for a specific type of exercise.

### Power and sample size estimate

The primary outcome is the HADS-total score at T1 (post-intervention). Based on a recent large RCT analyzing the effects of an MBI on the HADS in people with PD [13], we expect a moderate effect size (*d* = 0.48). This is also in accordance with a recent review of 44 meta-analyses investigating the effects of MBIs in different clinical populations, reporting effect sizes between 0.45 and 0.75 after an MBI when compared to care as usual [10]. Considering an effect size of 0.48, a comparison of two groups of 70 subjects would yield 80% power with a two-sided alpha of 0.05. We corrected our power for correlations between the covariate (HADS at T0) and outcome measure (HADS at T1), given our planned statistical model where we will include HADS at T0 as a covariate (see below). Assuming a conservative correlation (r) of 0.5 between these two measures, a sample size of *n* = 53 [70 × (1-r^2^)] patients per group is required [45]. Considering a potential drop-out of 15%, we will include 62 individuals per group. This sample size allows us to detect an absolute difference in HADS score of 3.1, which exceeds the minimal clinically important difference for the HADS in people with PD [24]. This will also allow us to demonstrate group effects with an effect size of > 0.50 for our secondary outcomes [46, 47].

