#### Recruitment

Patients will be recruited via three sources:

Attending clinicians at the outpatient clinic of the Radboudumc are asked to preselect patients they see during consultation or during a multidisciplinary meeting. In addition, we will recruit patients treated by neurologists in surrounding hospitals (for example in Den Bosch, Arnhem and Tiel). Attending neurologists will give information about the study and initial inclusion criteria. Only patients that show interest will receive more information about the study.We will contact patients that gave permission to be approached for new scientific studies about PD during their participation in previous studies in our center.The online platform ParkinsonNEXT (https://www.parkinsonnext.nl*)* will be used, through which people with PD can easily sign up for research projects. The ParkinsonNEXT website contains a webpage with general information about our project, including background information and the possibility to register directly. In addition, we will send an open invitation to participate in our study via ParkinsonNEXT to all registered patients living close to Nijmegen.

If people are interested to participate, the researchers will provide them with information and will invite them to complete the online screening questionnaires to check their eligibility. If the patient is interested and eligible, they will receive the participant information letter. A week later, the researcher will call to provide more information and answer remaining questions if necessary. Afterwards, the patient can give verbal consent and the first visit is planned. During the first visit, the procedure, details of the study and obligations of the participant and the clinical research team will be clearly explained to all patients once more, and written informed consent is obtained. Only subjects who can give legal consent will be included. Participants will be recruited in multiple study cohorts of 10–16 patients each. Accordingly, groups of ~ 5–8 patients will simultaneously participate in each study arm (exact numbers depend on the randomization algorithm).

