## Discussion

The MIND-PD trial is a prospective RCT investigating the short and long-term clinical and biological effects of MBCT in people with PD. The primary goal of this trial is to identify whether MBCT can effectively reduce symptoms of depression and anxiety in people with PD, as compared to care as usual. Beyond that, we aim to explore the effects of MBCT on: (a) *motor symptom severity*, (b) *stress biomarkers*, such as cortisol (in hair and saliva) and stress-related brain activity (fMRI before and after a strong stressor: socially evaluated cold pressor test), and (c) *PD progression biomarkers*, such as structural integrity of the substantia nigra and locus coeruleus (neuromelanin-sensitive MRI, diffusion MRI). Finally, we will explore the mechanisms underlying the effects of chronic and acute stress on PD symptoms (e.g. tremor, using accelerometry), by means of the clinical, neuroimaging and biochemical assessments at baseline. Insight into the mechanisms underlying stress and stress reduction in PD may pave the way to new treatment development.

MIND-PD adopts a large-scale and multidisciplinary approach, including psychological, neurological and neuroscientific assessments. Also, MBCT is a well-documented intervention, which, if proven to be effective, can be implemented readily on a broad scale. Other strengths of this trial include the large sample, statistically powered to detect a clinically meaningful difference on our primary endpoint. Also, we are the first to explore long term (> 3 months) effects of an MBI in PD, which allows us to not only identify relevant symptomatic effects of the intervention, but to begin to explore possible disease modifying effects as well [7]. Comprehensive outcome measures, including state of the art neuroimaging and markers of the biological stress response, will further provide unique insights into the cerebral and biochemical mechanisms of stress (reduction) in PD, which are unknown to date [7].

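### The stated 80% power and 3.1-point detectable difference assume independent patients; nothing is allowed for clustering within the MBCT therapy groups.

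*Protocol article*

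**What the plan says.** The section on power and sample size works with a standardised effect ("Considering an effect size of 0.48"), for which "a comparison of two groups of 70 subjects would yield 80% power with a two-sided alpha of 0.05". It then takes credit for baseline adjustment ("Assuming a conservative correlation (r) of 0.5 between these two measures"), multiplying 70 by 1 − r² to reach 53 per group. It finishes with drop-out: "Considering a potential drop-out of 15%, we will include 62 individuals per group". This size is said to allow detection of a 3.1-point HADS difference. The SD behind 3.1 is not given.

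The Interventions section (MBCT) says the training is delivered to groups of 8–10, mixing trial participants with other patients. Under Recruitment, "groups of ~ 5–8 patients will simultaneously participate in each study arm". The statistical section on the primary outcome specifies an ANCOVA of HADS at T1 on group, baseline HADS, age and gender. It provides for a cohort random effect only if the ICC is significant, in the text on the secondary mixed models. The Discussion lists as a strength that the sample is "statistically powered to detect a clinically meaningful difference on our primary endpoint".

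**The concern.** Patients taught together by the same teacher, in the same sessions, may end up with more similar outcomes than patients taught separately. The MBCT arm mean is then less precise than its number of patients suggests. The protocol acknowledges this dependence in its analysis section, but its sample size has only two adjustments: the covariate and drop-out. The chain is complete from 70 to 62, so no allowance for clustering is hidden in it.

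Two statements depend on this: the 80% power, and the 3.1 points as the difference the trial can detect. If either is optimistic, the Discussion's description of the sample is optimistic too. Leaving the cluster out of the primary model does not recover the loss. It moves the problem from power to the false-positive rate.

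**Working it through.** **Inputs from the protocol article.** d = 0.48; two-sided alpha 0.05; power 80%; r = 0.5, so the residual variance factor is 1 − 0.25 = 0.75; 15% drop-out; 62 per arm; about 5–8 study patients per arm per cohort (m).

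**Assumed.** The ICC among patients in the same MBCT group, on the covariate-adjusted outcome: 0.01 to 0.10. The document gives no value.

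**1. The plan's own figures.**
- 70 per arm, d = 0.48: power 80.5% (t-test).
- 70 × 0.75 = 52.5, rounded to 53. At 53 per arm with r = 0.5, power is 80.7% (t) or 81.4% (normal approximation); at 52 it is 79.9% (t).
- 52.5/0.85 = 61.8, rounded to 62; conversely 62 × 0.85 = 52.7 completers.
- 3.1/0.48 gives an implied SD of 6.46 points.

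The chain reproduces for independent patients. On its own inputs it leaves about one percentage point to spare.

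**2. Adding therapy-group clustering.** Only the MBCT arm is treated in groups. Each cohort contains both arms, so effects shared by a whole cohort largely cancel. With n completers per arm:

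SE² = 0.75 × [(1 + (m − 1)·ICC) + 1]/n, in units of SD²

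Power = Φ(0.48/SE − 1.96)

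Detectable difference at 80% power = (1.96 + 0.84) × SE × 6.46

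Variance inflation relative to independence is V = [2 + (m − 1)·ICC]/2.

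Example with n = 53, m = 8, ICC = 0.05: SE² = 0.75 × 2.35/53, SE = 0.182; 0.48/0.182 − 1.96 = 0.67; power 74.9%; detectable difference 3.30 points.

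| ICC | V, m = 5 to 8 | Power, m = 5 to 8 | Detectable difference (points) |
|---|---|---|---|
| 0 | 1.00 | 81.4% | 3.04 |
| 0.01 | 1.02–1.04 | 80.7–80.1% | 3.07–3.10 |
| 0.02 | 1.04–1.07 | 79.9–78.8% | 3.10–3.15 |
| 0.05 | 1.10–1.18 | 77.7–74.9% | 3.19–3.30 |
| 0.10 | 1.20–1.35 | 74.0–69.0% | 3.33–3.54 |

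**3. Where 80% is lost.** Setting power to 80% and solving gives 2 + (m − 1)·ICC = 2.074, so ICC = 0.074/(m − 1): 0.019 for m = 5 and 0.011 for m = 8.

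**4. Few groups.** 53/8 to 53/5 means about 7–11 MBCT groups. If the test's degrees of freedom reflect that number (Satterthwaite), power at ICC 0.05 is about 70–75% rather than 75–78%.

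**5. If the primary ANCOVA ignores the groups.** The model's standard error is then too small by a factor √V, and the true type I error is about 2 × [1 − Φ(1.96/√V)]. This gives 6.2–7.1% at ICC 0.05 and 7.4–9.2% at ICC 0.10.

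**The case against.** The strongest reply is that the shortfall is conditional, and that some inputs may be cautious.

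- **No ICC is documented.** At 0.01 power stays at 80–81%, and at 0.02 the loss is immaterial. This stands. A reader might infer that 62 per arm simply fails to deliver 80%; the documents do not support so flat a statement.
- **r = 0.5 is called conservative.** If r were 0.6 (an assumed value), power at ICC 0.05 with 53 completers would be 81–84%. This stands as a possibility, but the precision from r = 0.5 has already been used to cut 70 to 53, and the plan commits to no higher value.
- **Drop-out by T1 may be below 15%.** The Discussion ties drop-out risk to the 12-month follow-up, whereas the primary endpoint is at two months. With all 62 evaluable, power at ICC 0.05 is 81–84%. This also stands, though the protocol's own planning figure is 15%.
- **Drop-out also shrinks the groups.** Taking 15% off 5–8 gives about 4.3–6.8 completers per group, and power at ICC 0.05 of about 76–78%. This narrows the range but does not remove the loss.
- **The protocol provides a cohort random effect.** It does so conditionally, beside the secondary models, and it adds nothing to the sample size.

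A second tempting inference is that, because 3.1 points is said to exceed the minimal clinically important difference (MCID), the trial is underpowered for that difference and the text is therefore wrong. The text does not bear this out. It says only that the target is larger than that threshold, claims no 80% power at the threshold itself, and does not give its value.

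**Conclusion.** The point holds in conditional form. The 80% power and the 3.1 points are correct if MBCT participants are independent. They are overstated if the therapy-group ICC exceeds about 0.01–0.02, given 53 completers per arm, r = 0.5, groups of 5–8 and clustering in the MBCT arm only. At an ICC of 0.05 the cost is about 4–6 percentage points against the 81.4% that the same approximation gives without clustering. At 0.10 it is about 7–12 points. A few points more are lost if the degrees of freedom reflect the number of groups. An unadjusted primary analysis would instead carry a type I error of about 6–7% (ICC 0.05) or 7–9% (ICC 0.10).

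This is not an arithmetic error: every step from 70 to 62 reproduces. The defect is an unstated independence assumption that does not fit the group delivery described elsewhere in the same article. Its size rests entirely on an ICC that the document does not supply.

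**What to change.** Keep 62 per arm. In the power section, state the assumed therapy-group ICC, the cluster size and the SD behind 3.1 points (about 6.5 if derived from 3.1/0.48). Replace the single figure with a range, for example: *with 53 completers per arm, r = 0.5 and 5–8 study patients per MBCT group, power for d = 0.48 is about 75–78% at a therapy-group ICC of 0.05 (79–80% at 0.02, 69–74% at 0.10).* Say whether the figure refers to a primary model with or without a term for the therapy group; without one, the nominal power comes with an inflated type I error. Give the detectable difference on the same basis, and qualify the Discussion's statement about power to match.

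The cost is a change of wording and a slightly less favourable stated power. No extra patients are needed.

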## Methods: data management and statistical analyses

### Data management & confidentiality

All personal data will be handled in compliance with the EU General Data Protection Regulation. In all documents, subjects will be identified by an identification code to maintain pseudonymity (pseudonymisation entails to work with an identifier (a key-file) which allows the link between individuals and their data). The pseudonymisation key-file will be stored in an access restricted folder on the Donders file server, separately from the experimental data. Any personal data will be deleted as soon as it is no longer needed. Questionnaires and experimental data will be managed in CastorEDC, a username and password protected data capture system. All data will be stored on the Donders Institute infrastructure and archived on the Donders repository for 15 years upon study completion. Biochemical data will be destroyed upon completion of the trial. A data management plan further describing the location and access of study data, coding methods, and archiving of data has been approved by the Board of Directors of the Radboudumc.

### Statistical analyses

All analyses will be performed on an intention to treat basis. Longitudinal analysis (> 2 timepoints) will be performed with linear mixed models. Missing data will be imputed if necessary and possible.

#### Primary outcome

To determine whether MBCT can reduce symptoms of anxiety and depression in people with PD, our *primary analysis* will test the effects of GROUP (MBCT vs. CAU) on the HADS-total after treatment (T1). Specifically, an analysis of covariance (ANCOVA) will be used with HADS score at T1 as dependent variable and GROUP as fixed factor. Age at T0, gender and HADS at T0 will serve as covariates. *Secondary analyses* will explore the consolidation of treatment effects across TIME (T0 vs. T1 vs. T2) using mixed models (fixed effects: time, group, time*group; random intercept for SUBJECT). In case of a significant intraclass correlation coefficient, we will add COHORT as a random effect to account for clustering within intervention cohorts. Potential moderators of the treatment effect, such as cognitive impairment (MoCA at T0), disease severity (defined as time since diagnosis made by a neurologist), or age may be explored to identify subgroups of patients that particularly benefit from the intervention. Also, mediators of the effect, such as mindfulness skills (FFMQ), self-compassion (SCS), or rumination (RRS) may be tested, to explore psychological mechanisms underlying the effect of MBCT on symptoms of anxiety and depression.

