**Questionnaires**										
Anxiety and depression (HADS)^1^	X		X			X			X	
Perceived stress (PSS)	X		X			X			X	
Rumination (RRS)	X		X			X			X	
Self-compassion (SCS)	X		X			X			X	
Self-efficacy (GSES)	X		X			X			X	
Positive appraisal style (PASS)	X		X			X			X	
Mindfulness skills (FFMQ)	X		X			X			X	
Perceived social support (F-SozU K6)	X		X			X			X	
Quality of life (PDQ-39)	X		X			X			X	
Motor and non-motor experiences of daily living (MDS-UPDRS Ib, II)	X		X			X			X	

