**MBCT arm only**										
Mindfulness adherence (MAQ)			X		X	X	X	X	X	

^1^ Primary outcome

Study timepoints are at baseline (T0) two months after baseline (T1) and 12 months after baseline (T2). HQ = home questionnaire.

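### The long-term HADS model uses a random intercept alone over unequally spaced visits and leaves out month 6, so its 12-month standard error is probably somewhat too small (minor)

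*Protocol article*

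**What the plan says.** In the protocol article, Statistical analyses, Primary outcome, the primary test is an ANCOVA of HADS at T1. The secondary analysis is to "explore the consolidation of treatment effects across TIME (T0 vs. T1 vs. T2") with a mixed model specified as "fixed effects: time, group, time*group; random intercept for SUBJECT". One addition is conditional on a significant intraclass correlation: "we will add COHORT as a random effect to account for clustering within intervention cohorts".

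Table 1 lists "Anxiety and depression (HADS)^1" as a home questionnaire at months 0, 2, 6 and 12. The block restricted to the MBCT arm contains only "Mindfulness adherence (MAQ"), so both arms complete the HADS at month 6. The article describes no analysis of that measurement.

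**The concern.** A random intercept with independent residuals implies the same variance at each visit and the same correlation between any two visits. The three visits lie at months 0, 2 and 12, so the pairs are 2, 10 and 12 months apart. Correlation between repeated symptom scores usually falls with the interval. Entry also requires a HADS total above 10 (Study population), which may compress the variance at T0 relative to later visits. When the structure is wrong, the model gives every pair of visits the same standard error, although the true ones differ.

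This is the only stated HADS analysis beyond T1, and the Discussion presents effects beyond 3 months as a novelty of the trial. Too small a standard error at 12 months tilts that analysis towards false positives. Leaving out month 6 also means the model cannot tell an effect that has faded by mid-year from one that fades later.

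**Working it through.** **Plan's own figures.** No power or precision is stated for the long-term model. The sample size in Power and sample size estimate does reproduce: d = 0.48 with 70 per group gives power 0.805; 70 × (1 − 0.5²) = 52.5, rounded to 53; 52.5/0.85 = 61.8, rounded to 62.

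**Inputs.** From that section: 53 analysed per group, r(T0,T1) = 0.5, and SD = 3.1/0.48 = 6.46. All other correlations are assumed.

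**Formulas** (complete data, equal variances, n per arm). For the group difference in change between visits j and k:

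- true SE = √[4·SD²·(1 − r_jk)/n]
- random-intercept SE = √[4·SD²·(1 − r̄)/n], with r̄ the mean of the three correlations
- ratio = √[(1 − r̄)/(1 − r_jk)]
- type I error ≈ 2·[1 − Φ(1.96 × ratio)]

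**Example.** With r = 0.50 (T0,T1), 0.30 (T1,T2) and 0.27 (T0,T2), r̄ = 0.356. The model SE is 1.42 for every contrast. The true SE is 1.25 for T1−T0 and 1.51 for T2−T0. The ratios are 1.135 and 0.941.

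| Assumed r: T0,T1 / T1,T2 / T0,T2 | r̄ | T2−T0 ratio (type I) | T1−T0 ratio | T2−T1 ratio |
|---|---|---|---|---|
| 0.50 / 0.50 / 0.50 | 0.500 | 1.000 (5.0%) | 1.000 | 1.000 |
| 0.50 / 0.38 / 0.37 | 0.418 | 0.962 (5.9%) | 1.079 | 0.972 |
| 0.50 / 0.30 / 0.27 | 0.356 | 0.941 (6.5%) | 1.135 | 0.956 |
| 0.50 / 0.21 / 0.18 | 0.298 | 0.927 (6.9%) | 1.185 | 0.944 |
| 0.70 / 0.53 / 0.51 | 0.582 | 0.926 (7.0%) | 1.180 | 0.947 |
| 0.70 / 0.45 / 0.42 | 0.523 | 0.905 (7.6%) | 1.261 | 0.932 |
| 0.50 / 0.03 / 0.02 | 0.182 | 0.911 (7.4%) | 1.279 | 0.919 |
| 0.50 / 0.60 / 0.40 | 0.500 | 0.913 (7.4%) | 1.000 | 1.118 |
| 0.70 / 0.60 / 0.50 | 0.600 | 0.894 (8.0%) | 1.155 | 1.000 |
| 0.60 / 0.50 / 0.30 | 0.467 | 0.873 (8.7%) | 1.155 | 1.033 |

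The last three rows let scores settle after T1. In the first of them the 10-month correlation exceeds the 2-month one, so it is not pure decay.

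**Unequal variance.** Suppose selection at entry cuts the T0 variance to 40% or 60% of its unselected value. In the last three rows the T2−T0 ratio then becomes 0.90 to 0.94 (type I error 6.4% to 7.9%): softened, not removed. With a constant correlation of 0.6 before selection, T2−T1 becomes 0.96 to 0.97 (5.7% to 6.0%).

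**What month 6 adds to T2−T0** (unstructured covariance, 62 per arm). With complete data and r = 0.50/0.30/0.27, the SE is 1.399 with or without month 6: when each arm has its own mean at every visit, another visit carries no information on this contrast. With 9 of 62 per arm missing T2 but present at month 6, it falls from 1.470 to 1.465 (0.3%). Across the patterns with constant or falling correlation (first seven rows), the gain is 0.0% to 0.6%.

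**Month 6 without a new covariance.** Keeping the random intercept and adding month 6 moves the T2−T0 ratio from 0.941 to 0.933 in the same example, which is slightly worse.

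**The case against.** The strongest reply is that the 12-month correlations are not in the document, so the error is hypothetical. Constant correlation gives none, and the sign for T2−T1, arguably the contrast closest to consolidation, changes with the pattern chosen (ratios 0.92 to 1.12). This stands, and it makes the size conditional. It does not rescue the structure, which has no room for the correlations to differ. The COHORT term models similarity between patients, not correlation over time within a patient.

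A second reply is that the article defines three measurement timepoints, words this analysis as exploratory and may leave detail to an analysis plan not shown. That limits the weight of the point. But the time levels and the random effect are stated here, so this is a choice made rather than a detail left out.

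A reader might infer more than the document supports:

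- **That omitting month 6 makes the 12-month test less precise.** It does not to any useful degree, as shown above. Even at about 20% dropout, a variance ratio of 0.978 is about 1% of the SE (√0.978 = 0.989).
- **That averaging month 6 and T2 recovers about 20% of the variance.** Under assumed correlations (0.7 between them, 0.45 and 0.40 with T0) the baseline-adjusted variance is 27.9 against 35.1 for T2 alone. But this is a different estimand, and it could hide waning between months 6 and 12.
- **That the other questionnaires share the fault.** The Clinical assessments paragraph of the analysis section names GROUP and TIME for them without listing time levels or a random intercept, so month 6 is not excluded there.
- **That the general sentence on imputing missing data is part of the problem.** It is a separate matter of the kind usually left to the analysis plan.

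**Conclusion.** The point holds in limited form and is minor. The stated model imposes one correlation and one variance on unequally spaced visits, and it leaves the month-6 HADS unanalysed. Over the assumed non-constant patterns the SE is about 4% to 13% too small for T2−T0 (type I error about 6% to 9%) and 0% to 28% too large for T1−T0. For T2−T1 it may err modestly in either direction. With complete data the point estimates are unaffected. With constant correlation and equal variances the error is zero. The primary ANCOVA at T1 and the sample size are untouched. The loss from omitting month 6 is knowledge of the course between months 2 and 12 and slight support for missing data, not precision at T2.

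**What to change.** In the secondary HADS analysis, replace the random intercept alone by an unstructured within-patient covariance, or keep it and use robust standard errors. Add month 6 as a level of TIME for the HADS, and report the group effect at T1, month 6 and T2. Make the two changes together: the covariance change corrects the standard errors, and month 6 supplies the time course. Retain the conditional COHORT term as planned.

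The cost is wording only, fixed before the data are analysed. The month-6 HADS is already scheduled, and an unstructured covariance over four visits needs 10 parameters instead of 2, which is manageable with 124 patients.
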